#### “Intervention” group

All participants receive the high-dose cholecalciferol (vitamin D_3_) supplement in a single oral intake on the day of inclusion (Mylan; 75008 Paris, France). Cholecalciferol is packaged in a drinking vial of 2 mL containing 200,000 IU. Thus, participants in the Intervention group take two vials at once, to reach the studied total dose of 400,000 IU. Vitamin D is ideally taken during food intakes because vitamin D is lipophilic and therefore better absorbed with fat. Such high dose is expected to quickly raise the serum 25(OH)D concentration above 75 nmol/L [30], which is not expected with lower doses [23]. This is all the more important in that, based on the knowledge of vitamin D non-skeletal effects, it appears that raising serum 25(OH)D concentrations above 75 nmol/L is necessary to obtain antiviral effect [4]. Finally, it has to be quoted that the chosen dose of 400,000 IU does not reach the dose of 500,000 IU that has been previously associated with side effects [31]. In addition, participants in the Intervention group will not take other vitamin D supplements for 45 days and will therefore receive the equivalent of a daily dose of 8900 IU/day over the period, less than the toxic dose of 10,000 IU/day [28].

#### “Comparator” group

All participants receive the standard-dose cholecalciferol (vitamin D_3_) supplement in a single oral intake on the day of inclusion (Mylan; 75008 Paris, France). The treatment is packaged in a drinking vial of 2 mL containing 50,000 IU. Thus, participants in the Comparator group take one vial, to reach the studied total dose of 50,000 IU, in accordance with the maintenance treatment recommended in 2020 by the French Osteoporosis Research and Information Group (GRIO) [32]. The appearance and the number of drinking vials varying between the two arms, the study is open-labeled and both the investigators and the participants know which supplementation dose is taken.

We have chosen not to use a placebo in the study because it would not be legitimate in older adults since (i) 80 to 100% of non-supplemented older adults have hypovitaminosis D [4], (ii) hypovitaminosis D is accompanied by a high number of potentially serious acute and chronic diseases that are associated with higher mortality in COVID-19 patients [3, 4], and (iii) an international scientific society recommends vitamin D supplementation in primary prevention of COVID-19 in older adults [33]. Based on previous literature [27], we have also considered unlikely that the placebo effect of taking high-dose vitamin D is able to prevent death from COVID-19, even if our open-label study will not eliminate this plausibility.

Enrolled participants are also provided with oral and written information that they should not be prescribed medication containing vitamin D outside of the trial for the duration of the study (Comparator group) and up to 45 days for the Intervention group.

### Planned eligibility criteria

#### Inclusion criteria

People are eligible to participate if they are 65 years and over, if they have a SARS-CoV-2 infection diagnosed within the preceding 3 days by RT-PCR and/or chest CT scan, and if they have at least one worsening risk factor (age ≥ 75 years, or SpO2 ≤ 94% in room air, or PaO2/FiO2 ≤ 300 mmHg). Participants must be covered by or having the rights to medical care insurance. Participants must also have given and signed an informed consent form to participate in the trial (or informed consent form obtained from the trusted person, or emergency inclusion procedure in the context of lockdown, as appropriate).

#### Non-inclusion criteria

The following non-inclusion criteria are considered: organ failure requiring admission to intensive care, SpO2 ≤ 92% despite oxygen therapy > 5 L/min, life expectancy < 3 months, any reason preventing follow-up at 28 days, treatment with vitamin D supplementation during the preceding month (with the exception of supplements providing 800 IU or less vitamin D per day), contraindications to the use of vitamin D supplements (active granulomatosis [sarcoidosis, tuberculosis, lymphoma], history of calcium lithiasis, known hypervitaminosis D or hypercalcemia, known intolerance to vitamin D), enrolment in another simultaneous clinical trial, and deprivation of liberty by an administrative or judicial decision.

### Recruitment/consent procedures

Participants are identified from patients with COVID-19 who were diagnosed in each hospital and/or nursing home recruiting center. The 10 recruiting centers are all located in France and include Angers University Hospital, Bordeaux University Hospital, Le Mans Hospital, Lille University Hospital, Limoges University Hospital, Nantes University Hospital, Nice University Hospital, Saumur University Hospital, Saint-Etienne University Hospital, and Tours University Hospital. The participation of 4 additional French centers is under study (Château-Gontier Hospital, Lyon University Hospital, Public Assistance Hospital of Paris – Broca Hospital, Rennes University Hospital). Once a potential participant is identified and meets the eligibility criteria, the investigating physician provides the patient and relatives written and oral information on the study in an understandable language and obtains written consent to take part in the study in line with the trial standard operating procedures. When possible, fully informed consent is obtained from the patient. When a patient is unable to give fully informed consent, agreement to participate in the study is obtained from the trusted person, and the patient is not enrolled if s/he refuses or shows significant distress. If it is impossible for the trusted person to sign the consent due to nationwide lockdown, an emergency inclusion procedure may be conducted and will be accompanied by a consent returned by post as soon as possible. In case of refusal to participate in the study, the investigating physician will record the cause of non-participation in the study and copy it in the “Registry of non-eligible and eligible patients.”

### Assessments

Study assessment measures will be applied at baseline prior to randomization, at day 7 (± 1 day), day 14, and day 28. All measures in the study are usually carried out systematically in every patient admitted to the recruiting centers. Experience has shown that this operational mode is feasible and appreciated by patients and their relatives and has never caused a breakdown in care so far [34]. For this reason, the number of measures is not expected to exacerbate the loss to follow-up. Phone calls are planned to keep in touch with the participants. Trial completion is defined as completion of 28 days or discontinuation of follow-up for any cause.

#### Primary outcome measure

The primary outcome measure is all-cause mortality within 14 days of inclusion. Such follow-up time has the merit of including the mortality risk linked to the cytokine storm that usually occurs between the 7th and 10th day after infection [1], the clinical expression of which is fatal ARDS. Moreover, this objective outcome measure does not give rise to monitoring or measurement bias despite the open-label design.

#### Secondary outcome measures

The secondary outcome measures are (i) all-cause mortality within 28 days of inclusion and (ii) the changes of WHO’s OSCI scale for COVID-19 between baseline and day 14 and between baseline and day 28 [29].

#### Blood sample collection procedures

All participants are tested for 25(OH)D concentration at baseline and day 7 (± 1 day). Blood tests are done by a clinical research nurse. Serum 25(OH)D concentration is measured with radioimmunoassay (RIA) kits in each recruiting center. RIA kits recognize both vitamins D_2_ and D_3_. With this method, there is no interference of lipids, which is often observed in other non-chromatographic assays of 25(OH)D. The intra- and interassay precisions are respectively 5.2% and 11.3% (range in normal adults aged 20–60 years, 75–310 nmol/L). Creatinine, calcium, and albumin (to estimate corrected calcemia) are also measured at baseline and day 7 (± 1 day) with standard laboratory methods.

#### Safety parameters

The safety assessment parameters are:
Clinical: asthenia, vertigo, headache, anorexia, nausea and vomiting, polyuria-polydipsia, lumbar or right hypochondrium pain in case of biliary or renal colic revealing calcic lithiasis (objectified by ultrasound in the case of clinical suspicion)Biological: serum calcium, albumin (to estimate corrected calcemia), and creatinine concentrations at baseline and day 7 (± 1 day). The finding of hypercalcemia gives rise to appropriate care and triggers further complementary non-specific examinations to find the cause of hypercalcemia for which vitamin D supplementation could not be held responsible at first [3].

### Statistics

#### Sample size calculation

The trial aims to recruit 260 patients divided into 2 groups of 130 patients. Based on previous literature, the expected death rate in the standard-dose vitamin D group is estimated at 20% in this population with worsening risk factors [35]. A total of 125 participants per group should be involved to demonstrate, under a bilateral hypothesis, a between-group absolute difference in all-cause mortality risk of 12% with an alpha risk of 5% and a power of 80%. Such target is consistent with one previous study in an intensive care unit reporting a 17% mortality rate reduction in patients who received high-dose vitamin D compared to a placebo [27]. Taking into account the loss to follow-up (estimated at 5%), it is necessary to include a total of 260 subjects (130 per group).

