#### Analyses

The effect of high-dose vitamin D supplementation compared to standard-dose vitamin D supplementation will be determined using evaluation criteria, which are the mortality rates and the changes in OSCI score within 14 and 28 days of inclusion, using respectively the chi-square test or exact Fischer test, and independent samples *t* test or Mann-Whitney *U* test, as appropriate. An interim analysis of 100 participants is planned. It will focus on the primary outcome measure (i.e., all-cause mortality within 14 days of inclusion) with a *P* value of 0.001 used as the significance threshold for stopping the study. The final analysis of the primary outcome measure will use the *P* value of 0.0498 as the significance threshold (Peto-Haybittle method).

The proportions of participants with at least one serious adverse event within 28 days of inclusion will be compared using the chi-square test (or exact Fisher test if necessary). Survival curves will be plotted from baseline to day 28 using the Kaplan-Meier method, and a Cox proportional hazards model will be used to compare clinical outcomes between groups. The log-linearity assumptions will be checked for each quantitative variable introduced in the Cox models, and proportional hazards assumption will be checked for each variable to confirm adequacy for the Cox models.

Any exploratory analyses here will use multivariate logistic and proportional hazards regression. In addition, the stratification criterion for randomization will be also taken into account in the multivariate models. Excessive subgroup analyses can give rise to misleading results, and therefore, all subgroup investigations will be interpreted cautiously. In particular, subgroup analysis will be conducted depending on the severity of hypovitaminosis D at baseline and at day 7.

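### Recruiting 130 per group does not cover the assumed 5% loss on the plan's own requirement of 125 evaluable; power falls about one point short of 80%

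*Protocol article*

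**What the plan says.** All the figures are in the protocol article, under Statistics, Sample size calculation. The control rate is set there: "the expected death rate in the standard-dose vitamin D group is estimated at 20% in this population with worsening risk factors". The target is an absolute reduction of 12 points, hence 20% against 8%, at two-sided 5% and 80% power. The requirement is put this way: "A total of 125 participants per group should be involved to demonstrate, under a bilateral hypothesis". The recruitment total then follows: "Taking into account the loss to follow-up (estimated at 5%), it is necessary to include a total of 260 subjects (130 per group".

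The Analyses section compares mortality "using respectively the chi-square test or exact Fischer test", as appropriate, with a final threshold of 0.0498 after one interim look at 0.001. The Design section gives 1:1 allocation.

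**The concern.** Three stated figures cannot all hold: 125 evaluable per group needed, 5% lost, 130 per group recruited. The conflict needs no choice of sample size formula, because it lies in the step from 125 to 130.

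What is at stake is the power claimed at the design effect. The Ethical considerations section warns of low power only for effects smaller than 12 points, which implies that 12 points itself is covered at 80%. A non-significant result would be read against that figure, so it should be right on the plan's own loss assumption.

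**Working it through.** **Inputs** (Sample size calculation, Design and Analyses): p1 = 0.20, p2 = 0.08, difference d = 0.12, two-sided alpha 0.05 (final threshold 0.0498), power 80%, 1:1 allocation, 5% loss, 130 recruited per group. The chi-square test is taken without continuity correction; this is an assumption, as the article does not say.

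**1. Reproducing 125.** With z = 1.96 and 0.8416, (1.96 + 0.8416)² = 7.849.

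- Arcsine: h = 2(arcsin √0.20 − arcsin √0.08) = 0.354; n = 2 × 7.849 / h² = 125.4.
- Unpooled: n = 7.849 × (0.16 + 0.0736) / 0.12² = 127.3.

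The stated 125 is thus reproduced approximately.

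**2. Allowance for loss.**

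- Evaluable after loss: 130 × 0.95 = 123.5 per group, 247 in total. This is 1.5 per group below 125.
- Recruitment needed: 125 / 0.95 = 131.6, so 132 per group and 264 in total, against 260.
- Loss that 130 does cover: (130 − 125) / 130 = 3.8%.

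**3. Power of the chi-square test.** Exact power is the sum of the binomial probabilities of all pairs of death counts (20% and 8%) for which the test is significant.

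| Evaluable per group | Threshold 0.05 | Threshold 0.0498 |
|---|---|---|
| 123 | 79.2% | 79.2% |
| 124 | 79.5% | 78.8% |
| 125 | 79.2% | 79.2% |
| 127 | 79.9% | 79.9% |
| 128 | 80.2% | 80.2% |
| 130 | 80.9% | 80.9% |

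The small reversals between 123 and 125 come from the discreteness of the counts. Over the sizes enumerated (122 to 135), 80% is first reached at 128 and is kept from there on.

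**4. Approximations at 123.5 per group (alpha 0.05).**

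- Pooled: 77.9%
- Unpooled: 78.8%
- Arcsine: 79.4%

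Every method falls below 80% after the assumed loss. The gap runs from 0.6 points (arcsine) to 2.1 points (pooled). By exact enumeration it is 0.5 to 1.2 points, depending on the size (123 or 124) and the threshold.

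**The case against.** The strongest reply is that this is rounding. The recruited total is 4 patients short of 264, or 1.5%. Power moves by about a point, far less than it would if the assumed 20% control rate were off. Vital status at day 14 may be known for nearly everyone, and with 128 of 130 evaluable per group exact power is still 80.2%. The article also calls for larger trials if the result is not significant. All of this stands as to size. It does not remove the inconsistency: the plan itself assumes 5% loss, and on that assumption its own requirement is not met.

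A reader might infer more, and the documents do not support it:

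- *That 125 is itself wrong and 131 are needed.* The figure of 131 comes from the pooled normal approximation. The test itself reaches 80% at 128, and 125 is close to the arcsine result, with power of 79.9% by that formula and 79.2% by exact enumeration. An article may leave the formula to the full protocol, so its absence is no fault. Totals built on 131, such as 138 per group after loss, fall with it.
- *That 80% holds only if nobody is lost.* Two lost per group still leaves 80.2%.
- *That power is about 73%, because Fisher's test is mentioned.* That test is named for use where appropriate. With about 0.14 × 123.5 = 17 deaths expected per group, the chi-square test is the one that applies.

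**Conclusion.** The point holds as a minor arithmetic error. The allowance for loss was rounded down, so 130 per group does not preserve the stated 125 at 5% loss. Power at the design effect is then about 79% instead of 80%: a shortfall of about one point, and about two on the least favourable approximation.

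This rests on the plan's own 20% and 8%, on the full 5% loss occurring equally in both groups, on lost patients leaving the analysis of the primary outcome, and on the uncorrected chi-square test. The 0.0498 threshold changes almost nothing. It would be wrong to conclude that the trial is materially underpowered for a 12-point difference.

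**What to change.** Replace the last sentence of the sample size paragraph with a statement of this kind: *130 per group gives about 81% power by the chi-square test if 14-day vital status is known for all participants, and about 79% with the assumed 5% loss (about 123 per group).* Drop the statement that 260 patients absorb 5% loss at 80% power.

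The cost is one or two sentences and a stated power about one point lower under the assumed loss. Recruitment, design and analysis do not change. If the sponsor prefers to keep the 125 and the 5% allowance as they stand, the consistent total is 264, but a gap of this size does not call for extra patients.

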#### Analyses

The effect of high-dose vitamin D supplementation compared to standard-dose vitamin D supplementation will be determined using evaluation criteria, which are the mortality rates and the changes in OSCI score within 14 and 28 days of inclusion, using respectively the chi-square test or exact Fischer test, and independent samples *t* test or Mann-Whitney *U* test, as appropriate. An interim analysis of 100 participants is planned. It will focus on the primary outcome measure (i.e., all-cause mortality within 14 days of inclusion) with a *P* value of 0.001 used as the significance threshold for stopping the study. The final analysis of the primary outcome measure will use the *P* value of 0.0498 as the significance threshold (Peto-Haybittle method).

The proportions of participants with at least one serious adverse event within 28 days of inclusion will be compared using the chi-square test (or exact Fisher test if necessary). Survival curves will be plotted from baseline to day 28 using the Kaplan-Meier method, and a Cox proportional hazards model will be used to compare clinical outcomes between groups. The log-linearity assumptions will be checked for each quantitative variable introduced in the Cox models, and proportional hazards assumption will be checked for each variable to confirm adequacy for the Cox models.

Any exploratory analyses here will use multivariate logistic and proportional hazards regression. In addition, the stratification criterion for randomization will be also taken into account in the multivariate models. Excessive subgroup analyses can give rise to misleading results, and therefore, all subgroup investigations will be interpreted cautiously. In particular, subgroup analysis will be conducted depending on the severity of hypovitaminosis D at baseline and at day 7.

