**Methods:**

The COVIT-TRIAL study is an open-label, multicenter, randomized controlled superiority trial. Patients aged ≥ 65 years with COVID-19 (diagnosed within the preceding 3 days with RT-PCR and/or chest CT scan) and at least one worsening risk factor at the time of inclusion (i.e., age ≥ 75 years, or SpO2 ≤ 94% in room air, or PaO2/FiO2 ≤ 300 mmHg), having no contraindications to vitamin D supplementation, and having received no vitamin D supplementation > 800 IU/day during the preceding month are recruited. Participants are randomized either to high-dose cholecalciferol (two 200,000 IU drinking vials at once on the day of inclusion) or to standard-dose cholecalciferol (one 50,000 IU drinking vial on the day of inclusion). Two hundred sixty participants are recruited and followed up for 28 days. The primary outcome measure is all-cause mortality within 14 days of inclusion. Secondary outcomes are the score changes on the World Health Organization Ordinal Scale for Clinical Improvement (OSCI) scale for COVID-19, and the between-group comparison of safety. These outcomes are assessed at baseline, day 14, and day 28, together with the serum concentrations of 25(OH)D, creatinine, calcium, and albumin at baseline and day 7.

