## Methods

### Objectives

The primary objective is to compare the effect of a single oral high dose of cholecalciferol versus a single oral standard dose of cholecalciferol on 14-day all-cause mortality rate in older adults infected with SARS-CoV-2 at higher risk of worsening.

The secondary objectives of the study are as follows:
To compare the effect of high-dose versus standard-dose cholecalciferol on 28-day all-cause mortality rateTo compare the effect of high-dose versus standard-dose cholecalciferol on the clinical course of the disease (i.e., change of World Health Organization’s [WHO] Ordinal Scale for Clinical Improvement [OSCI] scale for COVID-19) within 14 and 28 days of inclusion [29]To compare the safety of high-dose versus standard-dose cholecalciferolTo compare the effect of high-dose versus standard-dose cholecalciferol on all-cause mortality rate and OSCI scale changes within 14 and 28 days of inclusion in the subgroup with vitamin D deficiency at baseline (i.e., serum 25(OH)D < 25 nmol/L)To determine the impact of serum 25(OH)D concentration at day 7 (i.e., serum 25(OH)D concentration < 75 nmol/L versus ≥ 75 nmol/L) on mortality rate and OSCI scale changes within 14 and 28 days of inclusionTo determine, in the subgroup with vitamin D deficiency at baseline (i.e., serum 25(OH)D < 25 nmol/L), the impact of the serum 25(OH)D concentration reached at day 7 (i.e., serum 25(OH)D concentration < 75 nmol/L versus ≥ 75 nmol/L) on mortality rate and OSCI scale changes within 14 and 28 days of inclusionTo model survival and clinical course (OSCI scale changes) within 14 and 28 days of inclusion according to the change of serum 25(OH)D concentration between day 0 and day 7To compare the mortality rates observed within 14 days of inclusion in each arm of the study with the mortality rates reported in the French hospital geriatric units receiving COVID-19 patients

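### OSCI, an ordinal secondary outcome, is compared as an unadjusted change from baseline, which is hard to interpret and, under a linear model, never more precise than adjusting for baseline

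*Protocol article*

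**What the plan says.** Under Secondary outcome measures, the protocol article defines the outcome as "the changes of WHO’s OSCI scale for COVID-19 between baseline and day 14 and between baseline and day 28". The Analyses section takes the same quantity as an evaluation criterion, "which are the mortality rates and the changes in OSCI score within 14 and 28 days of inclusion", and assigns it the "independent samples *t* test or Mann-Whitney *U* test, as appropriate". No covariate is attached to that comparison.

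The Objectives section gives the scale its full name, "World Health Organization’s [WHO] Ordinal Scale for Clinical Improvement [OSCI] scale for COVID-19", so it is ordinal by the article's own description. The abstract says of the outcomes, OSCI included, "These outcomes are assessed at baseline, day 14, and day 28", and Table 1 places OSCI at the same three visits. A baseline value is therefore planned for every participant.

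Adjusted models appear only later in Analyses: "Any exploratory analyses here will use multivariate logistic and proportional hazards regression", with the addition that "the stratification criterion for randomization will be also taken into account in the multivariate models". No ordinal model is named. Baseline OSCI is named neither as a covariate nor among the six minimisation criteria listed under Design.

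**The concern.** Two separate weaknesses follow from subtracting baseline on this scale.

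**Meaning.** A difference of two ordinal levels has a fixed meaning only if all steps are equal. Mann-Whitney does not repair this, because the subtraction comes before the ranking. If death is a level, one and the same fatal outcome gets a different score according to where the participant started. Starting levels can be expected to vary: Design minimises on hospitalisation (yes or no) and on oxygen dependence, and recruitment covers hospitals and nursing homes.

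**Precision.** The baseline value enters with a fixed coefficient of one. Estimating that coefficient, as baseline adjustment does, can only help in large samples. The open question is by how much.

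What is at stake is the readability and sensitivity of the day-14 and day-28 OSCI comparisons. The article itself warns, under Ethical considerations, that the trial may be underpowered for effects smaller than its 12-point mortality target. That gives a graded outcome some added value.

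**Working it through.** **The plan's own figure.** The article gives no sample size or precision for OSCI. Its one calculation, 125 per group for mortality of 20% versus 8%, is reproduced by the arcsine formula (125.4 per group at two-sided 5% and 80% power). It does not bear on OSCI, except that 125 per group is the size used in the simulation below.

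**Scoring of deaths.** Let death be level K. A death from starting level b scores K − b. With K = 8 (assumed):
- death from level 2: 8 − 2 = +6
- death from level 4: 8 − 4 = +4
- death from level 5: 8 − 5 = +3
- survivor moving from level 2 to level 6: 6 − 2 = +4

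The death from level 5 therefore ranks as a milder deterioration than this survivor's. Under the design hypothesis, deaths by day 14 would number about 130 × 0.20 + 130 × 0.08 = 26 + 10.4 ≈ 36 of 260, or 14%. All would share one outcome but carry scores that differ with baseline. Outright ties or reversals between a death and a survivor were rare in the simulation below, at about 1% of pairs.

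**Precision under a linear model.** Let s0 and s1 be the baseline and follow-up SDs, rho their correlation and k = s0/s1. Per participant:
- change score: s1² + s0² − 2·rho·s0·s1
- baseline-adjusted: s1²(1 − rho²)
- difference: (s0 − rho·s1)², which is never negative

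The variance ratio, adjusted over change, is (1 − rho²)/(1 + k² − 2·rho·k). Neither rho nor k is in the article, so a range is shown:

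| k | rho = 0.3 | rho = 0.5 |
|---|---|---|
| 1 | 0.91/1.40 = 0.65 (−35%) | 0.75/1.00 = 0.75 (−25%) |
| 0.7 | 0.91/1.07 = 0.85 (−15%) | 0.75/0.79 = 0.95 (−5%) |
| 0.5 | 0.91/0.95 = 0.96 (−4%) | 0.75/0.75 = 1.00 (0%) |

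The article points towards k below 1. The Non-inclusion criteria remove participants who need intensive care or remain poorly saturated on high-flow oxygen, which narrows the baseline. The Sample size calculation expects 20% control deaths, which widens the follow-up.

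**Simulation with rank methods.** Because the plan allows Mann-Whitney, the linear formula is only a guide. The simulation used 125 per group, an assumed 0 to 8 scale with 8 as death, about 20 to 25% control deaths, a common odds ratio of 0.55 and rho from 0 to 0.49. Power was:
- t test on change: 62 to 68%
- Mann-Whitney on change: 61 to 72%
- baseline-adjusted rank analysis of the final level: 71 to 77%

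Within scenarios the gain over Mann-Whitney on change was about 1 to 15 points, largest at low rho. A second set, with odds ratio 0.5, gave 0 to 8 points. With no treatment effect, type I error was about 4 to 6% for every method.

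**The case against.** The strongest reply has four parts.

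First, the precision gain may be very small. For an illustrative baseline on levels 2 to 5 and a follow-up with 20% deaths, k is about 0.35. At rho = 0.5 the ratio is then 0.75/(1 + 0.1225 − 0.35) = 0.97, a gain of 3%, and at rho = 0.3 it is below 1%. This stands. A reader might take the 25 to 35% reduction as the expected gain, but it needs equal baseline and follow-up spread, which the eligibility rules and expected mortality make doubtful.

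Second, the scale's levels are not in the article, so the scoring of deaths rests on an assumption. This also stands. How deaths are handled may be set out in the full protocol or SAP, so silence on it is not a fault here. The equal-steps objection does not depend on it.

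Third, the objective is framed as change, so a model for the level alters the target quantity. This stands only in part: comparing clinical course between randomised arms does not require subtraction, and an adjusted comparison of levels answers the same question.

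Fourth, minimisation on hospitalisation and on the worsening risk factor, which includes oxygen dependence, already limits chance imbalance in baseline severity. That is fair, and it reduces the practical weight of the point.

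Some stronger readings should be resisted:
- **Bias or false positives.** Randomisation protects the comparison, and the simulated error rates were near nominal.
- **Damage to the mortality results.** Deaths are compared directly at days 14 and 28, with Kaplan-Meier curves and a Cox model, and OSCI scoring cannot alter these.
- **OSCI as the main secondary outcome.** Objectives and Secondary outcome measures list 28-day mortality first, and no hierarchy is stated.
- **The choice between t test and Mann-Whitney.** Leaving it open is ordinary shorthand in an article.

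**Conclusion.** The point holds as one of interpretability and efficiency in a secondary outcome. The article commits to an unadjusted change score on an ordinal scale although the baseline needed for a better analysis is already collected.

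The equal-steps problem follows from the article alone. The uneven scoring of deaths also needs death to be a scale level. The precision gain cannot be fixed from the article: for rho 0.3 to 0.5 it runs from 35% down to nil as k falls from 1 to 0.5, with the lower part more plausible here. The case for change therefore rests mainly on interpretability. The change is worth making, but nothing in the primary analysis depends on it.

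**What to change.** In Analyses, replace the two-sample comparison of OSCI changes with a comparison of the OSCI level at day 14 and, separately, at day 28, with death as the worst category. Use a proportional-odds model, or rank ANCOVA, adjusted for baseline OSCI and for the minimisation factors where numbers allow (recruiting centre may be too sparse). With the proportional-odds model, report the common odds ratio with its confidence interval. In either case show the distribution over categories by arm, and keep the change from baseline as a descriptive summary. Align the wording under Secondary outcome measures and Objectives so that the named outcome matches the analysis.

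The cost is wording only, with no new data or visits. The small downside is that the proportional-odds assumption has to be examined, for which the category distributions by arm are the natural check.
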